## Methods

### Design

This study is a prospective multi-center randomized controlled trial with two parallel groups, comparing an intervention group to a control group with equal (1:1) randomization. Patients will be recruited from various head and neck cancer centers in the Netherlands in which TLs are performed. Patients in all participating centers who are found eligible will be asked to participate in this study by their treating head and neck surgeon, speech therapist or nurse specialist/practitioner at the last consultation prior to discharge, at follow-up visit or by mail plus telephone. After signing informed consent, patients will be randomly assigned to the intervention or control group. The baseline assessment takes place before randomization, with follow-up assessment immediately after the intervention or control period (i.e. at 3 months follow-up) and at 6 months follow-up (Fig. 1). Reasons for drop-out will be registered. This study has been approved by the Medical Ethics Committee of the VU University Medical Center.

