### Outcome assessment

For this study, different patient reported outcome measures will be collected at baseline, immediately after the intervention or control period (i.e. at 3 months follow-up) and at 6 months follow-up. Completion of the outcome measures is expected to take on average 30 min.

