### Sample size

In a previous study of Rinkel et al. [8] a standard deviation of 21 on the SWALQOL, the primary outcome measure in this study, was found. In addition, a difference in improvement of 12 points was found to be clinically meaningful. Based on a power of 80 %, a significance level of 5 % and a standard deviation of 21, in total 100 patients are needed (50 patients per intervention arm), to demonstrate a difference in improvement of 12 points between the intervention and control group at 6 months follow-up. Results will be analyzed according to the intention-to-treat principle and all drop-outs, when possible, will be approached for follow-up measurements.

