### Statistical analyses

All analyses will be performed using the IBM Statistical package for the Social Science (SPSS) version 22 (IBM Corp., Armonk, NY USA) and STATA version 12.1 (StataCorp LP, Texas, USA). Descriptive statistics (e.g. frequencies, percentages, means and standard deviations or medians and (interquartile) ranges) will be generated for all socio-demographic and clinical characteristics and outcome measures. Chi-square tests, independent *t*-tests and Mann-Whitney tests (in case of non-normality of the measure) will be used to analyze whether randomization resulted in comparable patient groups. Analyzes will be performed according to the intention-to-treat principle. A *p*-value < .05 will be considered significant.

Independent *t*-tests will be used to measure differences in swallowing quality (SWAL-QOL), speech quality (SHI), shoulder function (SDQ) and quality of life (EORTC QLQ-C30 and H&N35) between the intervention and control group at follow-up measurements. Linear mixed models and generalized estimating equations, with fixed effects for group and measurement and their two-way interaction and a random effect for subject, will be used to compare longitudinal changes in both groups over time.

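### The longitudinal model's subject random effect, read in the usual way, assumes equal correlation between all visits; the 6-month change contrast should not depend on that, and a GEE has no such term

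*Protocol article*

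**What the plan says.** The protocol article, Statistical analyses, plans two kinds of between-group comparison for SWAL-QOL and the main secondary scales.

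- Cross-sectional: "Independent *t*-tests will be used to measure differences in swallowing quality (SWAL-QOL") and the other scales between the arms at the follow-up measurements.
- Longitudinal: "Linear mixed models and generalized estimating equations", both described by the clause "with fixed effects for group and measurement and their two-way interaction and a random effect for subject". Their purpose is stated: they "will be used to compare longitudinal changes in both groups over time".

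Outcome assessment sets three measurements: baseline, then "immediately after the intervention or control period (i.e. at 3 months follow-up) and at 6 months follow-up". Sample size takes 50 patients per arm "to demonstrate a difference in improvement of 12 points between the intervention and control group at 6 months follow-up".

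The article states no residual covariance for the mixed model, no working correlation or type of standard error for the GEE, and no standard deviations or correlations by visit.

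**The concern.** The clause names one source of within-patient dependence. A random intercept with independent, equal-variance residuals gives compound symmetry: one variance for all visits and one correlation for all pairs of visits. The standard error of any change contrast then comes from a within-patient variance pooled over all three pairs, not from the pair being compared.

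The pair that matters most is baseline and 6 months, because the trial is sized on improvement at 6 months. Of the two planned approaches, only the longitudinal model compares change as such.

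The design gives some reason to doubt equal correlation. Patients may be approached "at the last consultation prior to discharge, at follow-up visit or by mail plus telephone", and up to 5 years after surgery. The Randomization section stratifies at 6 months after surgery, partly because recent patients may still receive postoperative (chemo)radiation. If recent patients recover at different rates after baseline, their baseline score will predict the 6-month score less well than the 3-month score does. The 6-month contrast would then have too small a standard error, too narrow an interval and a false-positive rate above 5%.

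Separately, a GEE is a marginal model. It handles dependence through a working correlation and has no random effect, so the shared clause cannot be fitted literally for that half.

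**Working it through.** **The plan's own figure.** The inputs in Sample size are "Based on a power of 80 %, a significance level of 5 % and a standard deviation of 21", with a difference of 12 points. Two-sided testing is assumed, as the article does not say.

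n per arm = 2 × (1.960 + 0.842)² × 21² / 12² = 48.1, so 49 per arm (98 in total). With the noncentral t distribution, power is 79.96% at 49 and 80.8% at 50 per arm. The stated 50 per arm reproduces.

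**Inputs for the check.** SD 21 and 50 per arm come from the article. Using SD 21 at every visit, complete data and all correlations are assumptions; hence a range.

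**Formulas.** With complete data and a random intercept:

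- change variance used by the model = 2 × (mean variance − mean covariance)
- true variance of the 6-month change = var(0) + var(6) − 2 cov(0,6)
- with equal SDs, SE ratio (model/true) = √[(1 − mean r) / (1 − r(0,6))]
- type I error = 2 × [1 − Φ(1.96 × ratio)]

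**Worked case**, r(0,3) = 0.6, r(3,6) = 0.7, r(0,6) = 0.5. The mean r is 0.6.

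- Model: 2 × 441 × 0.4 = 352.8, SD 18.8.
- True: 2 × 441 × 0.5 = 441, SD 21.0.
- Ratio = √(0.4/0.5) = 0.894; type I error = 2 × [1 − Φ(1.753)] = 8.0%.
- SE of the between-arm contrast = SD × √(2/50) = 0.2 × SD: 3.76 in the model against 4.20. The 95% half-width is 7.4 points where 8.2 is needed.

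**Range of assumptions, 6-month change contrast:**

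| r(0,3) / r(3,6) / r(0,6) | SE ratio | Type I error |
|---|---|---|
| equal (0.5 or 0.6 throughout) | 1.000 | 5.0% |
| 0.65 / 0.65 / 0.55 | 0.923 | 7.1% |
| 0.6 / 0.7 / 0.5 | 0.894 | 8.0% |
| AR(1), 0.5 | 0.882 | 8.4% |
| AR(1), 0.7 | 0.852 | 9.5% |
| 0.5 / 0.8 / 0.4 | 0.850 | 9.6% |
| AR(1), 0.8 | 0.839 | 10.0% |
| 0.6 / 0.6 / 0.65 | 1.047 | 4.0% |

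Under AR(1) with 0.7, the 3-month contrast errs the other way: ratio √(0.37/0.30) = 1.111, type I error 3.0%.

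Unequal variances alone matter little. With all correlations 0.6, SDs of 18/20/22 give 5.2%, and 21/21/25 give 5.8%.

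**Simulation** (20,000 trials per case, 50 per arm) agrees with the closed form and adds the other analyses:

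- Joint two-degree-of-freedom group-by-measurement test from the random-intercept model, under 0.6/0.7/0.5, 0.5/0.8/0.4 and AR(1) 0.7: between 5.1% and 6.3% over two runs.
- 6-month contrast with an unstructured covariance: about 5% throughout.
- GEE with robust standard errors, under equal 0.6, 0.65/0.65/0.55 and 0.7/0.7/0.5: 5.5% to 5.6%.
- Independent t-test at 6 months, same three cases: 5.1% to 5.2%.

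**The case against.** A reader might infer that the standard error and p-value of the 6-month change are wrong. The documents do not support that, for these reasons.

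- Nothing in the documents shows that compound symmetry fails. There is one SD and no correlation. Whether there is an error, and in which direction, depends on assumed values; under equal correlations it is zero. This stands in full.
- The article does not say that the random effect is the only dependence term. A mixed model can also carry a structured residual, and an article may leave that to a fuller document. This stands in part: the article does state a dependence structure, and its ordinary reading is compound symmetry, so a later plan would have to amend the sentence and not merely fill a gap.
- The intervention is not itself a reason for a lower baseline correlation. Under the null hypothesis it has no effect, and a constant effect leaves the within-arm covariance unchanged. Wide variation in time since surgery mainly makes patients differ from one another. This stands; what remains is uneven recovery among recent patients, and the article does not say how many there will be.
- The article names no single 6-month contrast from the model, and the joint interaction test is only slightly inflated. This also stands, but the sample size is tied to improvement at 6 months, so that contrast is likely to be read.
- The t-tests need no within-patient covariance and keep their level. True, although as worded they compare scores at follow-up rather than improvement.
- The clause can be read as giving the random effect to the mixed model and clustering by subject to the GEE. That is a fair reading. The GEE wording needs correcting but invalidates no p-value.

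**Conclusion.** The point holds in conditional form. The usual reading of the clause makes the 6-month change contrast rely on equal variances and correlations over three visits, an assumption that the trial does not need and that could fail among recently operated patients. If the baseline to 6-month correlation is clearly the lowest, the standard error is about 8% to 16% too small and the type I error about 7% to 10%. These figures assume SD 21 at each visit, complete data, 50 per arm and correlations that the documents do not supply. The t-tests, and a GEE with robust standard errors, stay close to 5%. The random effect in the GEE is a plain specification error in wording, independent of any assumed figure. This is an inexpensive improvement to the plan, not a demonstrated flaw in its results.

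**What to change.** Split the sentence into two specifications.

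- Linear mixed model: group, visit as a categorical factor and their interaction, with an unstructured 3x3 within-patient covariance in place of the random intercept. Take the 6-month group difference in change from this model.
- GEE, if kept: remove the random effect, cluster on subject, and state a working correlation (for example exchangeable) with robust standard errors.

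Cost: a change of wording, with no new data or patients. The unstructured matrix has six covariance parameters against two for the random intercept, estimated from up to 300 observations (100 patients × 3 visits). The 6-month interval may become slightly wider; in the worked case the half-width goes from 7.4 to 8.2 points, which is the width that case requires.

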### Randomization

Patients will be randomized to the intervention or control group by an independent person, stratified for 1) time since TL (≤6 months after TL vs. > 6 months after TL) to distinguish patients who are recently treated and who may in some cases receive postoperative (chemo)radiation from patients who completed their treatment longer ago; 2) neck dissection (not treated with a neck dissection versus treated with a neck dissection); and 3) TL indication (primary TL or salvage TL) in blocks of two and four using an automatically created randomization list. Although this is a multicenter study, we chose not to stratify for study center, because head and neck cancer care is mainly centered in the University Hospitals in the Netherlands and highly protocolled via the Dutch Head and Neck Oncology Cooperative Group (NWHHT).

Patients randomized to the intervention group will be provided access to the guided self-help exercise program targeting speech, swallowing and shoulder problems built into the application ITwC as well as the self-care education program. Patients randomized to the control group will, in addition to usual care, also be provided access to the self-care education program, since we aim to investigate the effectiveness of the guided self-help exercise program only.

The guided self-help program ITwC will be provided by Internet [32] or as booklet plus DVD. Patients can choose themselves between these two formats. Both formats contain the same content (i.e. the same written instructions, images and videos are available).

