An incremental cost utility ratio (ICUR) will be calculated measuring the cost per gained quality-adjusted life year (QALY). The ICUR will be calculated by dividing the incremental costs by the incremental QALYs, using the formula: ICUR = (C_int_ - C_con_)/(QALY_int_ - QALY_con_). Total costs will be calculated using a societal perspective, including intervention costs, direct medical, direct non-medical and indirect non-medical costs. Direct medical and non-medical costs will be calculated by multiplying resource use by integral cost prices as presented in the CVZ guideline on cost studies [43]. Indirect non-medical costs will be calculated using the friction cost approach as recommended in the CVZ guideline [43]. Total QALYs will be calculated by using the utility scores linked to the various health states of the EQ-5D [40]; in essence the length of time a patient spends in a particular health condition is weighed by the corresponding utility. Missing data on direct medical, direct non-medical and indirect non-medical costs measured using the cost questionnaire and utilities measured using the EQ-5D will be imputed using multiple imputation. If necessary, the estimates of the cost difference, the QALY difference and the ICUR will be corrected for differences in baseline characteristics between the two groups. Since follow-up of the study is less than 1 year, we will neither discount costs nor effects. To assess uncertainty surrounding the findings, 5000 bootstrapped replications will be calculated and presented on a cost-utility plane. In addition, ICUR acceptability curves will be presented and sensitivity analyses will be performed focusing on uncertainty surrounding most important cost items.

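### Baseline adjustment of the QALY and cost differences is conditional on an undefined need; adjusting the QALY difference for baseline EQ-5D utility in every case would be markedly more precise at no extra data cost

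*Protocol article*

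**What the plan says.** All of this is in the protocol article.

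- **ICUR (Statistical analyses).** The ratio is defined from the plain between-arm differences: "The ICUR will be calculated by dividing the incremental costs by the incremental QALYs".
- **QALY (same section).** It is a time-weighted utility: "the length of time a patient spends in a particular health condition is weighed by the corresponding utility".
- **Baseline correction (same section).** "If necessary, the estimates of the cost difference, the QALY difference and the ICUR will be corrected for differences in baseline characteristics". No criterion for necessity follows, and no covariate is named.
- **Baseline comparison (same section, opening paragraph).** Chi-square, t- and Mann-Whitney tests "will be used to analyze whether randomization resulted in comparable patient groups". The text does not link these tests to the correction rule.
- **Timing (Outcome assessment; Design).** The questionnaires are completed "at baseline, immediately after the intervention or control period (i.e. at 3 months follow-up) and at 6 months follow-up", and "The baseline assessment takes place before randomization".
- **Stratification (Randomization).** Allocation is "stratified for 1) time since TL (≤6 months after TL vs. > 6 months after TL", and also for neck dissection and for TL indication. Baseline utility is not a factor.
- **Size (Sample size).** "in total 100 patients are needed (50 patients per intervention arm".

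**The concern.** Under area-under-the-curve weighting, the baseline utility is one of the three terms that make up each patient's six-month QALY. It is also likely to predict the other two. A chance difference in baseline utility therefore enters the QALY difference twice: directly through its own term, and indirectly through the follow-up terms it predicts. The stratification does not balance it.

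The standard remedy is a regression on arm and baseline utility, whatever imbalance is seen. The article instead makes correction depend on a judgement after the data are in. If correction is skipped, the error due to the imbalance drawn stays in the QALY difference, and hence in the denominator of the ICUR, the cost-utility plane and the acceptability curves. If the choice is made by looking at the data, the analyst also has discretion over which estimate is reported. Cost-utility is named in the title and the aim of the trial, so the precision of this result matters.

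**Working it through.** **The article's own figure.** There is none for the cost-utility analysis. The one number taken from the plan is 50 per arm, and it reproduces for SWAL-QOL (two-sided 5%, 80% power, SD 21, difference 12): n = 2 × (1.960 + 0.842)² × 21² / 12² = 48.1, so 49 per arm. The exact t calculation gives 79.96% power at 49 and 80.8% at 50.

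**Inputs.**
- From the article: 50 per arm; utilities at 0, 3 and 6 months.
- Assumed, not in the article: trapezoidal interpolation; utility SD 0.25 at each time; equal correlation ρ between times, 0.5 to 0.7; complete data.

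**Step 1, weights.** Over half a year, QALY = 0.125·u0 + 0.25·u3 + 0.125·u6. Baseline carries 0.125/0.5 = one quarter of the weight.

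**Step 2, size of a chance imbalance.** SE of the baseline difference = 0.25 × √(2/50) = 0.05.

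**Step 3, shift of the unadjusted QALY difference.** Per unit of imbalance the expected shift is b = 0.125 + 0.375ρ.

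**Step 4, precision.** In units of the utility variance, Var(QALY) = 0.09375 + 0.15625ρ. Then R² on baseline utility = b²/Var(QALY), and the SE reduction from always adjusting is 1 − √(1 − R²).

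| ρ | b | shift at imbalance 0.05 | R² | SE, never adjusted | SE, always adjusted | reduction |
|---|---|---|---|---|---|---|
| 0.5 | 0.3125 | 0.0156 | 0.568 | 0.0207 | 0.0136 | 34% |
| 0.6 | 0.3500 | 0.0175 | 0.653 | 0.0217 | 0.0127 | 41% |
| 0.7 | 0.3875 | 0.0194 | 0.739 | 0.0225 | 0.0115 | 49% |

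For scale, 0.0175 QALY is worth 0.0175 × 20,000 = EUR 350 per patient at the willingness-to-pay value that the Discussion cites from another study. That value is not stated to be this trial's threshold.

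**Step 5, against conditional adjustment.** The plan does not say it will never adjust, so the fairer comparator is adjusting only when a 5% baseline t-test on utility is significant. In 20,000 simulated trials per correlation under the same assumptions, the SD of the estimated QALY difference was:

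| ρ | adjust only if significant | always adjust | reduction |
|---|---|---|---|
| 0.5 | 0.0190 | 0.0138 | 28% |
| 0.6 | 0.0197 | 0.0128 | 35% |
| 0.7 | 0.0202 | 0.0116 | 43% |

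The baseline test fires in about 5% of trials, as it must under randomization, so conditional adjustment recovers little of the available gain. The nominal 95% intervals under the conditional rule covered about 97%: too wide rather than too narrow.

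**Step 6, other assumptions.** At SD 0.20 and ρ = 0.7 the SE falls from 0.0180 to 0.0092. Across SD 0.15 to 0.30 and ρ 0.5 to 0.8, a one-SE imbalance shifts the unadjusted difference by 0.009 to 0.026 QALY. The percentage reduction in Step 4 does not depend on the SD.

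**The case against.** **The article does provide for correction.** This stands. A reader might infer that imbalance passes unchecked into the ICUR, but the sentence at issue allows for correcting all three quantities. The weakness is that it does so only on an undefined condition.

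**The trigger is not stated.** This stands too. A reader might infer that the baseline significance tests decide whether to correct. They are the only baseline comparison described and so a likely trigger, but nothing in the text says so. The point does not need that link: any trigger that depends on the observed imbalance has the same weakness in kind. Only the 28% to 43% figure is specific to a significance-test trigger.

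**The unadjusted estimate is unbiased, and the bootstrap reflects chance imbalance.** Correct over repeated randomization, and it rules out a claim of systematic bias. The 0.0175 shift at ρ = 0.6 also lies within one unadjusted SE (0.0217). A misleadingly narrow interval is not supported either, since the simulated coverage was conservative. What remains is error conditional on the imbalance drawn, lost precision and analyst discretion. The bootstrap displays that imprecision but does not reduce it, and the planned sensitivity analyses concern cost items.

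**A condensed article may leave this to a fuller document.** True of the covariate list and of how regression is combined with the bootstrap. It is not true of the conditional wording: the article states a rule, and a fuller document that always adjusted would contradict it.

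**The sizes rest on assumed inputs.** They do. The direction follows from how the QALY is built and from any positive correlation over time; the amounts depend on the assumptions listed.

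**Conclusion.** The point holds as a worthwhile improvement to a stated rule, not as an error that invalidates the analysis. The correction is conditional, the condition is undefined, and the one covariate that enters the QALY by construction is not named. Under trapezoidal QALYs, utility SD 0.25, correlation 0.5 to 0.7 and 50 complete cases per arm, always adjusting reduces the standard error of the QALY difference by 34% to 49% against no adjustment and by about 28% to 43% against test-then-adjust. A one-SE baseline imbalance moves the unadjusted difference by about 0.016 to 0.019 QALY.

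No figure can be given for costs, because the article says nothing about how baseline costs relate to later costs; the gain there is less certain. Only the cost-utility analysis is affected.

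**What to change.** In the cost-utility paragraph of Statistical analyses, delete the opening condition of the correction sentence and state that:

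1. the QALY difference is always estimated from a regression on arm and baseline EQ-5D utility, with the three stratification factors;
2. the cost difference is estimated likewise, with costs over the three months before baseline as the covariate;
3. both regressions are refitted within each imputation and each bootstrap replicate;
4. the ICUR, cost-utility plane and acceptability curves are computed from these adjusted differences.

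The unadjusted differences can be reported alongside.

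The cost is wording and analysis code. Baseline EQ-5D and cost questionnaires are already collected before randomization, so no patients, visits or items are added, and the sample size stays at 100. The change should be fixed before outcome data are examined.
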